## Background

Gestational diabetes (GDM) is defined as carbohydrate intolerance with onset or recognition during pregnancy [1]. GDM affects 7-14% of the pregnancies in the U.S. and the prevalence has increased 30-100% during the last decade [2]. A meta-analysis [3] of 20 studies reported that among women with GDM, the risk of developing diabetes postpartum was seven times higher than that in women with normoglycemic pregnancies. The Diabetes Prevention Program [4] (DPP) demonstrated that among people with impaired glucose tolerance, intensive lifestyle intervention reduced the risk of developing diabetes by 58% in parous women with or without a history of GDM whose pregnancies were approximately 12 years before enrollment [5]. Yet postpartum quality of care in women with GDM (e.g., glucose testing, counseling on lifestyle factors and weight management) is suboptimal [6,7]. Young women diagnosed with GDM often receive prenatal care from a team of providers in order to control blood glucose levels via diet, physical activity and medications. This focus on healthy practices may coincide with increased motivation for healthy behavior change out of concern for the infant. Continuing and adopting such lifestyle skills into early motherhood may reduce the risk of diabetes later in life in this high risk population.

We previously demonstrated the feasibility of a pregnancy and postpartum print/telephone-based lifestyle intervention based on the DPP curriculum [8]. The next step was to implement this intervention at the health system level to evaluate its translation into clinical practice. This article describes a cluster randomized intervention trial conducted among the 44 medical facilities of Kaiser Permanente Northern California (KPNC) that includes 2,320 pregnant women with GDM identified during a 12-month period. A cluster randomized trial design was selected because KPNC has a centralized print/telephone-based case management system for all pregnancies complicated by GDM across the 44 medical facilities [9]. By adapting our intervention for use in 22 randomly selected KPNC medical facilities, we can compare its effectiveness for weight management to KPNC’s usual care practices for women with GDM.

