### Eligibility and exclusion criteria

All 44 KPNC medical facilities serviced by the RPSC are included. Pregnant women receiving medical care at the 44 medical facilities with a diagnosis of GDM [13] between March 27, 2011 and March 30, 2012, and who are 18 years of age or older, are potentially eligible (n = 2,480). Women are excluded if they had a neonatal loss (n =18) or did not have any telephone contact with the RPSC during pregnancy (n = 142), leaving 2,320 eligible women. The postpartum telephonic intervention is introduced as a new program being offered by the RPSC to new mothers with a GDM history; therefore, contact with the RPSC and willingness to participate in a case management program for GDM offered by the health system during pregnancy is required.

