### Randomization

Given significant variation in the expected number of GDM cases per medical facility in a 12-month period (range: 3 – 247; mean = 57.5, sd = 50.3), randomization is blocked on medical facility size (i.e., expected number of annual cases of GDM: <25, 25–74, ≥75). We implemented a restricted randomization scheme [15], whereby we ensured an acceptable level of between–condition balance in expected racial/ethnic distributions and in number of women contacted for recruitment by an unrelated observational GDM study that was ongoing at the time of GEM study randomization. This was achieved by eliminating all allocations that did not meet specified balance criteria (i.e., maximum between-condition relative difference) from among all possible treatment allocations for the 44 medical facilities. After considering a variety of balance criteria scenarios, we chose a 20% within stratum and 10% overall balance criteria for each racial/ethnic group, and a 15% between condition balance on the expected number of GDM cases with recruitment attempts by the observational study. These criteria resulted in 44,631,615 acceptable allocations and good performance in terms of pairwise medical facility frequencies, with 95% of all clinic pairs (total of 946 pairs) randomized to the same condition with probabilities of 40% to 60% (designs resulting in many instances of cluster pairs never/rarely or always/often randomized to the same arm threaten study validity) [15].

With treatment conditions for enumerated allocations labeled as groups A and B, one allocation was randomly chosen via a random number generator, with the seed supplied by a non-study staff person (SAS® software function RANUNI) [16]. At a separate time and location, via a flip of a coin, another non-study staff person assigned group A and B to intervention/usual care groups, witnessed by the GEM study biostatistician ([name]).

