### Statistical analyses, power and sample size considerations

All analyses comparing the effectiveness of each intervention strategy on our primary and secondary outcomes will be by intent-to-treat, including all eligible study subjects with measurements at all available time points, as appropriate to the outcome; analysis of treatment differences will be by original treatment condition assignment, regardless of adherence. The two primary outcomes for this study are the achievement of the postpartum weight goals and change in weight. Analyses will utilize marginal regression models for estimation of population average intervention effects, with linear mixed regression in analyses of weight change and logistic regression with estimation via generalized estimating equations (GEE) in analyses of reaching the weight goal. These regression models account for the within medical facility correlation between patients and within person correlation among repeated measurements, for valid estimation of treatment effects and associated standard errors. Variation in treatment group differences over time will be examined via the introduction of appropriate cross-product (interaction) terms between groups and time.

At the planning stage of this study, we expected a total sample size of 2,432 women diagnosed with GDM in a given year at the 44 facilities, and that approximately 76% would have weight measured at/near 12 months postpartum. Minimum detectable differences in the proportion meeting weight goals ranged from 0.060 to 0.10, across the range in expected proportion meeting goal in the usual care condition (0.15 - 0.25) and across the range in expected intraclass correlation (0.01 - 0.05) [chi-square test for two proportions, two-sided test, α = .05, power = .80]. For our actual sample size of 2,320 eligible women with GDM at the 44 facilities and with an expected 70% with weight measured at or near 12 months, the minimum detectable difference in proportions ranges from 0.062 to 0.11. The minimum detectable difference in mean weight at 12 months postpartum ranged from .16 to .23 standard deviation units at the planning stage, with no change in detectable effect sizes with the slightly lower actual sample size and proportion with weight measured at or near 12 months. These calculations are conservative, given that primary analyses will utilize multiple weight measures per person via mixed effects regression analyses.

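### If the GEE test of goal attainment uses the usual uncorrected sandwich variance, 44 very unequal facilities give a type I error of about 6 to 8.5%, and the article names no correction

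*Protocol article*

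**What the plan says.** All of this is in the protocol article.

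- *Statistical analyses, power and sample size considerations* names the method for the binary primary outcome: "logistic regression with estimation via generalized estimating equations (GEE) in analyses of reaching the weight goal". It adds: "These regression models account for the within medical facility correlation between patients and within person correlation among repeated measurements", with the stated aim "for valid estimation of treatment effects and associated standard errors".
- *Eligibility and exclusion criteria* gives the number of clusters: "All 44 KPNC medical facilities serviced by the RPSC are included". *Background* gives the split: "By adapting our intervention for use in 22 randomly selected KPNC medical facilities", which leaves 22 for usual care.
- *Randomization* blocks on facility size, with the reason that begins "Given significant variation in the expected number of GDM cases per medical facility in a 12-month period". It gives the range as 3 to 247 and the moments as "mean = 57.5, sd = 50.3".
- The only significance level stated belongs to the power calculation: "chi-square test for two proportions, two-sided test, α = .05, power = .80".

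The article does not give the working correlation, the variance estimator, the reference distribution or any finite-sample correction. Nor does it say that no correction will be used.

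**The concern.** The sandwich variance is built from one squared score contribution per cluster, and its validity is a large-sample result in the number of clusters. With few clusters it fails in two ways. The fitted model pulls residuals towards zero, so the variance is biased downward. The variance estimate is also noisy, so a normal reference is too optimistic. Unequal cluster sizes make both worse, because larger facilities have more leverage.

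Goal attainment is one of two primary outcomes. If the default variance is used, its confidence interval is too narrow and its test exceeds the nominal 5%, so a result close to p = 0.05 could turn on this choice. The article's statement that the standard errors are valid would then not hold at this number of facilities.

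**Working it through.** **Inputs from the article.** 44 facilities, 22 per arm; expected size mean 57.5, SD 50.3, range 3 to 247; size strata <25, 25–74 and ≥75; usual-care proportion 0.15 to 0.25; ICC 0.01 to 0.05; 2,320 women with 70% measured at 12 months.

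**Step 1: reproduce the article's detectable differences.** Effective n per arm = (N × retention / 2) / [1 + (m − 1) × ICC], with m = N × retention / 44; then solve a two-proportion test for 80% power.

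- Planning: 2,432 × 0.76 = 1,848, so m = 42.0. ICC 0.01: 924 / 1.410 = 655, difference 0.059 at proportion 0.15. ICC 0.05: 924 / 3.050 = 303, difference 0.104 at proportion 0.25. The article states 0.060 to 0.10.
- Actual: 2,320 × 0.70 = 1,624, so m = 36.9. ICC 0.01: 812 / 1.359 = 597, difference 0.062. ICC 0.05: 812 / 2.795 = 290, difference 0.107. The article states 0.062 to 0.11.

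The figures reproduce, so the inputs have been read as intended.

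**Step 2: how unequal the facilities are.** CV = 50.3 / 57.5 = 0.875. When women are weighted equally, 44 such clusters carry roughly the information of 44 / (1 + 0.875²) = 44 / 1.765 ≈ 25 equal ones, or about 12 per arm.

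**Step 3: simulate under no treatment effect.** Facility sizes were fitted to the stated mean, SD and range and scaled to 1,626 women. Allocation was stratified by size, outcomes were beta-binomial, and there was one time point. Each scenario had 6,000 trials. The Monte Carlo standard error at a true 5% is √(0.05 × 0.95 / 6,000) = 0.28 points. Rejection rates (%) for the treatment-only logistic GEE, where KC is Kauermann-Carroll, MD is Mancl-DeRouen, and the SE ratio is average estimated SE over true SD:

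| Proportion | ICC | Working correlation | SE ratio | Uncorrected, z | Uncorrected, t | KC, t | MD, z |
|---|---|---|---|---|---|---|---|
| 0.15 | 0.01 | independence | 0.944 | 7.52 | 6.67 | 5.73 | 5.45 |
| 0.15 | 0.01 | exchangeable | 0.931 | 8.25 | 7.45 | 6.47 | 6.23 |
| 0.15 | 0.03 | independence | 0.930 | 8.05 | 7.25 | 6.52 | 6.22 |
| 0.15 | 0.03 | exchangeable | 0.967 | 6.67 | 5.87 | 5.27 | 5.25 |
| 0.15 | 0.05 | independence | 0.933 | 7.78 | 7.05 | 5.77 | 5.40 |
| 0.15 | 0.05 | exchangeable | 0.949 | 7.23 | 6.43 | 5.72 | 5.78 |
| 0.25 | 0.01 | independence | 0.942 | 7.37 | 6.63 | 5.55 | 5.35 |
| 0.25 | 0.01 | exchangeable | 0.942 | 8.23 | 7.28 | 6.12 | 6.00 |
| 0.25 | 0.03 | independence | 0.935 | 8.23 | 7.30 | 6.10 | 5.75 |
| 0.25 | 0.03 | exchangeable | 0.949 | 7.35 | 6.48 | 5.85 | 5.83 |
| 0.25 | 0.05 | independence | 0.920 | 8.33 | 7.43 | 6.23 | 5.83 |
| 0.25 | 0.05 | exchangeable | 0.957 | 7.13 | 6.15 | 5.38 | 5.45 |

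The uncorrected z test rejects in 6.7 to 8.3%. Even the lowest value is (6.67 − 5) / 0.28 ≈ 6 Monte Carlo standard errors above 5%. With size strata in the model it rejects in 7.6 to 9.5%; the article does not say whether the strata enter the model.

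Two further simulations on the same inputs bracket this. One (4,000 trials per scenario, gamma-distributed sizes) gave 6.9 to 8.3%. The other gave 7.3 to 8.6% under independence and 6.0 to 6.8% under an exchangeable working correlation. Together: about 6 to 8.5%.

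**Step 4: bias and noise both matter.** With SE ratio r, bias alone would give a rejection rate of 2[1 − Φ(1.96r)]. At r = 0.920 this is 7.1% against 8.33% simulated; at r = 0.967 it is 5.8% against 6.67%. The rest comes from noise in the variance estimate. This is why a t reference alone is not enough (5.9 to 7.5% in the table).

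**Step 5: corrected versions.** Mancl-DeRouen with t on 44 − 2 = 42 df gave 4.3 to 5.6% in one of the further simulations and 4.1 to 5.1% in the other. Kauermann-Carroll with t gave 5.0 to 6.4% and, in the table, 5.3 to 6.5%.

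**The case against.** The strongest reply is that the article never commits to the uncorrected version. GEE is an estimation method, and GEE with a Mancl-DeRouen variance is still GEE, so the remedy is compatible with the text as it stands. Variance estimators and degrees of freedom are details that an article commonly leaves to an analysis plan, and that plan is not shown. The validity sentence can also be read as explaining why clustering is modelled, not as vouching for one variance formula.

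Much of this stands. A reader might infer that the plan uses no small-sample correction and that the trial's true type I error is therefore 7 to 8%. The article supports neither statement: it is silent on the variance and the reference distribution, so the figures describe one possible implementation, though the customary one. What does not fall is that the article fixes GEE for a primary outcome and describes its standard errors as valid without qualification. On the article's own cluster numbers, that description is wrong for the customary implementation.

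Two limits on the calculation also stand. It covers one time point, not the planned repeated measures, and it omits the balance restrictions on race/ethnicity and on recruitment by the observational study. It would also overstate matters to say that a few facilities dominate. The largest has 247 of about 44 × 57.5 = 2,530 expected cases, or 9.8%, and blocking tends to spread large facilities over both arms. The inflation comes from general inequality among a moderate number of clusters.

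**Conclusion.** The point holds conditionally, with moderate confidence. If goal attainment is tested with the uncorrected sandwich variance and a normal reference, type I error is about 6 to 8.5% for a treatment-only model at one time point, depending on working correlation, ICC and proportion. In the tabulated simulation the standard errors are about 3 to 8% too small (ratios 0.967 to 0.920). The arithmetic is firm; what the trial will actually run is unknown.

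The result assumes facility sizes fitted to the stated mean and SD, uniform 70% measurement, beta-binomial clustering and size-stratified allocation. It concerns goal attainment only. Nothing was computed for the mixed model of weight change, so no conclusion extends to it. If the analysis plan already specifies a suitable correction, the point is closed.

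**What to change.** State, before treatment groups are compared, that the GEE analysis of goal attainment uses the Mancl-DeRouen bias-corrected sandwich variance with facility as the cluster unit, and a t reference on facilities minus facility-level parameters (42 df for a treatment-only model). Simulated type I error is then about 4 to 5.5%. Kauermann-Carroll with the same t reference is a weaker option (up to about 6.5%).

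As a check, run a randomization test that samples from the 44,631,615 acceptable allocations described under *Randomization*, including the coin flip that labelled the two groups. It respects the restricted design and needs no large-cluster approximation.

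The cost is one sentence and a software option, with slightly wider intervals. If the analysis plan already says this, confirming it is enough.

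### The stated minimum detectable differences treat the 44 facilities as equal in size, although the protocol reports a facility-size SD close to the mean; power at those differences is nearer 71–75% than 80% under the planned analysis.

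*Protocol article*

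**What the plan says.** The section on statistical analyses, power and sample size gives its basis as "chi-square test for two proportions, two-sided test, α = .05, power = .80". The usual-care proportion meeting the weight goal runs from 0.15 to 0.25 and the intraclass correlation (ICC) from 0.01 to 0.05. The current figures rest on an "actual sample size of 2,320 eligible women with GDM at the 44 facilities and with an expected 70% with weight measured"; the measurement meant is the one in the 12-month window. The result is that "the minimum detectable difference in proportions ranges from 0.062 to 0.11". For mean weight the section gives 0.16 to 0.23 SD at planning and reports no change for the actual sample. It prints no design effect and mentions no allowance for unequal facility size. It then adds: "These calculations are conservative, given that primary analyses will utilize multiple weight measures per person via mixed effects regression analyses".

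The Randomization section describes large differences between facilities in expected annual cases: a range of 3 to 247, with "mean = 57.5, sd = 50.3". It uses this variation only to block the randomization on size.

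**The concern.** In a cluster trial, unequal cluster sizes lower the effective sample size below what the equal-size design effect gives. The loss grows with the square of the CV of cluster size. Here the CV is 50.3/57.5 = 0.875. Blocking on size balances the arms but does not recover that information.

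If the power calculation ignored the variation, the printed differences carry less than 80% power for both primary outcomes. Readers use such ranges to judge what a null result can exclude, and here they would overstate the trial's sensitivity. The remark that the calculations are conservative adds to the reassurance but concerns a different component of variance.

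**Working it through.** **Inputs (all from the Protocol article).** Actual sample: 2,320 × 0.70 = 1,624 women, 812 per arm, m = 1,624/44 = 36.9 per facility. Planning: 2,432 × 0.76 ≈ 1,848 women, 924 per arm, m = 42.0. Two-sided α 0.05, power 0.80, usual-care proportion p = 0.15 to 0.25, ICC 0.01 to 0.05, CV = 0.875 (CV² = 0.765).

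**Formulas.** Effective n per arm = n/DE.

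- Proportions: two-proportion chi-square test, pooled variance under the null, no continuity correction, solved for the difference.
- Means: (1.960 + 0.842) × √(2·DE/n), in SD units.
- Equal facilities: DE = 1 + (m − 1)·ICC.
- Unequal facilities, women weighted equally: DE = 1 + ((1 + CV²)·m − 1)·ICC.
- Unequal facilities, efficient weighting: the equal-facility DE divided by RE = 1 − CV²·λ(1 − λ), where λ = m·ICC/(m·ICC + 1 − ICC).

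**Step 1: reproduce the protocol's figures with equal facilities.** Actual sample: DE = 1 + 35.9 × 0.01 = 1.36 and 1 + 35.9 × 0.05 = 2.80.

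| Figure | Computed | Stated |
|---|---|---|
| Proportion, actual | 0.0624 to 0.1066 | 0.062 to 0.11 |
| Proportion, planning | 0.0594 to 0.1043 | 0.060 to 0.10 |
| Mean weight, actual | 0.162 to 0.233 SD | no change from planning |
| Mean weight, planning | 0.155 to 0.228 SD | 0.16 to 0.23 SD |

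The low end of each proportion range is p = 0.15 with ICC 0.01; the high end is p = 0.25 with ICC 0.05. All agree to within rounding, the loosest being 0.0594 against 0.060. Neither unequal-size formula fits: for planning proportions they give 0.066 to 0.130 (women weighted equally) and 0.065 to 0.115 (efficient weighting), against the stated 0.060 to 0.10.

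**Step 2: add the CV, actual sample.**

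- Women weighted equally: DE = 1 + (1.765 × 36.9 − 1) × ICC = 1.64 at ICC 0.01 and 4.21 at ICC 0.05.
- Efficient weighting: λ = 0.272 and 0.660, RE = 0.849 and 0.828, DE = 1.359/0.849 = 1.60 and 2.795/0.828 = 3.37.

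| | Equal facilities | Efficient weighting | Women weighted equally |
|---|---|---|---|
| Detectable difference, proportion | 0.062 to 0.107 | 0.068 to 0.118 | 0.069 to 0.132 |
| Detectable difference, mean weight (SD) | 0.162 to 0.233 | 0.176 to 0.255 | 0.178 to 0.285 |
| Power at 0.062 (ICC 0.01) | 79.6% | 72.8% | 71.7% |
| Power at 0.11 (ICC 0.05) | 82.3% | 74.7% | 65.2% |
| Power at 0.16 SD (ICC 0.01) | 79.0% | 72.2% | 71.1% |
| Power at 0.23 SD (ICC 0.05) | 79.2% | 71.3% | 61.8% |

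**Step 3: sensitivity to the CV.** With CV 0.7 instead of 0.875, power is 74–75% at 0.062 and 71–78% at 0.11, depending on weighting.

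**Step 4: can repeated weights make up the loss?** They reduce person-level variance, not between-facility variance. The between-facility share of the equal-facility variance of an arm mean is m·ICC/DE: 0.369/1.359 = 27% at ICC 0.01 and 1.845/2.795 = 66% at ICC 0.05. Under efficient weighting, person-level variance would have to fall by about 23% (ICC 0.01) or 40% (ICC 0.05) to bring the variance back to the equal-facility value. With women weighted equally at ICC 0.05, the facility term alone, 1.765 × 36.9 × 0.05 = 3.26, exceeds the whole equal-facility DE of 2.80, so no number of repeated weights would do it.

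**The case against.** The strongest reply has four parts.

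**The worst figures do not describe the planned analysis.** A reader might take 0.132, 0.285 SD and power in the low 60s as the true position. Those values belong to an analysis that weights women equally. The protocol plans a linear mixed model for weight change and a GEE logistic model for the goal, both accounting for within-facility correlation. The mixed model gives women in large facilities less weight, and so does the GEE if its working correlation is exchangeable, which the article does not state. This stands: efficient weighting is the main case, and equal weighting of women is the less favourable bound.

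**The remark about being conservative may be partly right.** A reader might infer that it is false. The documents do not show that. The calculation counts only women with a 12-month weight, whereas the analysis takes all eligible women with measurements at any available time point. At ICC 0.01 about 73% of the variance is person-level, and there the gain could offset the loss. Assuming, for example, that 85–90% of women have at least one postpartum weight and that the effect is averaged over time, person-level variance falls to about 0.78–0.82 of the calculated value and power at ICC 0.01 returns to about 80%. Those percentages are not in the protocol, and the gain would be smaller for a contrast at 12 months alone. The remark is therefore unquantified, and qualifying it is enough.

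**The inputs are partly inferred.** No design effect is printed, and the CV comes from expected cases averaging 57.5 per facility (57.5 × 44 = 2,530), not from the women analysed. This limits the precision of the replacement figures. It does not explain the match in Step 1, and the shortfall persists at CV 0.7.

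**Nothing in the trial's conduct changes.** All 44 facilities and all eligible diagnoses in the window are already included. This limits the severity, but the printed figures remain inaccurate.

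**Conclusion.** Wrong as written. The printed ranges match an equal-facility calculation and disagree with the protocol's own account of facility size. With CV 0.875, the ranges are about 0.068 to 0.118 for the proportion and 0.18 to 0.26 SD for mean weight under efficient weighting, with power of about 71–75% at the printed differences: a shortfall from 80% of roughly 5 to 9 points. If women are weighted equally, the ranges are 0.069 to 0.132 and 0.18 to 0.29 SD, with power of about 62–72%.

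This rests on three assumptions: the equal-size design effect is inferred from reproduction, the CV of expected cases carries over to women with a 12-month weight, and the GEE gains from efficient weighting only with an exchangeable working correlation. The finding concerns what the calculation delivers as set out. It does not show that the final repeated-measures analysis must fall short of 80% power at low ICC, or that the trial needs more women.

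**What to change.** Restate the minimum detectable differences with the facility-size CV in the design effect, and name the weighting assumed: about 0.068 to 0.118 and 0.18 to 0.26 SD under efficient weighting, with 0.069 to 0.132 and 0.18 to 0.29 SD as the less favourable bound. If the CV among women with a 12-month weight is known, use it instead of 0.875.

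For the remark on conservatism, either give the expected gain from repeated weights and from women without a 12-month weight, with the correlation and completeness assumed, or add that the gain applies to person-level variance only and may not offset the unequal facility sizes.

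This is a change of wording and figures. Enrolment, randomization and analysis stay as they are; the only cost is that the stated sensitivity becomes less favourable.
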